## Background

Age is an important risk factor for vision impairment and blindness [1, 2]. Due to aging of the world population, an increase in older people with vision impairment is expected in the upcoming years [2–6]. In 2020, 1.1 billion people had distance vision impairment or uncorrected presbyopia worldwide. By 2050, this is expected to rise to 1.8 billion people [2]. The older population residing in care institutions and receiving home healthcare in the Netherlands experience a high prevalence of blindness and low vision, ranging from 20 to 25% [7, 8]. This is in line with the global prevalence of moderate to severe vision loss or blindness, for individuals aged 70 years or older, which is 22% and 5%, respectively [3], as well as self-reported data from nursing home facilities across eight European countries, reporting a 19.5% prevalence [9].

Vision impairment in older people is associated with lower quality of life and barriers to participate in society [5, 10–12]. It can also lead to health problems such as depressive symptoms, falls, and fractures [6, 12–17]. Furthermore, older adults with severe vision impairment can experience difficulties in obtaining health information due to the way the information is presented. Access to health information is necessary for making healthcare decisions and to follow up on healthcare recommendations [18].

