## Methods

### Study design and ethical approval

We will perform a cluster RCT to compare online eye screening, in addition to CAU, versus CAU. The eye screening will be guided by community nurses. Cost-effectiveness and cost-utility will be studied from a healthcare and societal perspective, including the impact on physical and mental health. We will map healthcare costs over a period of 1 year. The study will be performed in collaboration with three Dutch home healthcare organizations. The study protocol was approved by the Medical Ethics Committee of Amsterdam University Medical Centers (Amsterdam UMC), location VUmc in Amsterdam, the Netherlands. This study protocol was written according to the “Standard Protocol Items: Recommendations for Interventional Trial” (SPIRIT) reporting guidelines [30]. The SPIRIT checklist is added as an Additional file 1.

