### Randomization

Teams of community nurses (clusters), which will participate in the cluster RCT, will be randomized to either the intervention (eye screening in addition to CAU) or control group (CAU). As there are differences in the number of participants a team is able to include, we will group participating teams into matched pairs on the basis of number of participants to prevent imbalance between the group sizes. One researcher (VR) will use Castor to randomize the clusters, by using block randomization. Randomization of the clusters will be stratified by home healthcare organization to stimulate regional heterogeneity and to equally divide the additional burden on the organizations. This will be done after the community nurse has invited patients to participate in the study. Due to the nature of the intervention, community nurses and participants cannot be masked. Research assistants, who will perform visual acuity measurements and administer questionnaires during the follow-up assessments, will be masked. Participants are asked not to disclose the nature of their treatment allocation during the follow-up assessments. The research team will regularly check whether a research assistant is still masked by asking to guess to which trial arm a participant is allocated. Allocation to the intervention or control group will be communicated with the community nurses by email by an unmasked researcher.

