#### Primary outcome

The primary outcome is a clinically relevant change of 2 lines or more (exceeding measurement error) on the Colenbrander-1 M visual acuity chart between baseline and 12 months follow-up.

Visual acuity will be assessed in both groups for both eyes separately at baseline and after 6 months and 12 months follow-up, by trained research assistants. These measurements will be performed in participants’ homes and will not be connected in any way to the nurse-assisted web-based screening, and outcomes will not be communicated with patients. Research assistants will be trained according to a strict protocol. The Colenbrander 1-M chart has an occluder attached to it with a rope of 1 m length. Participants will be asked to sit on a chair in front of the chart that is fixed on a music stand and adjusted to the participant’s height. The research assistant makes sure that there is sufficient light and no inappropriate reflection of light on the chart. Participants will be allowed to wear their own spectacles, except for reading addition. In glasses with varifocal lenses, participants will be asked not to look through the reading addition but straight over it. The occluder is equipped with a correction of + 1D. The number of letters read correctly will also be converted to logMAR visual acuity. The baseline and 6-month interpretations of the results of the vision-related measurements will not be shared with the participant and community nurse [41].

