### Statistical analysis

A table will be presented showing baseline demographic and clinical characteristics for each group.

To determine the validity of the questionnaires that are used within this study population, item response theory models will be performed. These models incorporate the characteristics of questionnaire items and responses, rendering a more accurate representation of the score on the latent construct, increasing the validity of the used questionnaires and the accuracy of the obtained results.

To determine effectiveness, linear mixed models (LMMs) will be used for continuous outcomes and logistic generalized estimating equation (GEE) analyses for dichotomous outcomes, given the longitudinal structure of the data. This will be based on intention-to-treat (i.e., all data will be included independent of completion of the intervention, including uptake after referral). We will use group (intervention vs. control), time, and the interaction between group and time as predictors. *P*-values less than 0.05 will be considered statistically significant.

The cost-effectiveness from a healthcare and societal perspective of eye screening compared to CAU will be determined based on the primary (incidence of clinically relevant changes in visual acuity) and secondary outcomes. Cost-utility will be determined with quality-adjusted life-years (QALYs) based on the EQ-5D-5L. Bias-corrected and accelerated bootstrapping with 5000 replications will be used to calculate 95% confidence intervals around the mean difference in total costs between the two groups for both perspectives. Incremental cost-effectiveness ratios (ICERs) and incremental cost-utility ratios (ICUR) will be calculated, as well as cost-effectiveness curves. Bootstrapping will be used to estimate the uncertainty surrounding the ICERs, which will be plotted graphically on cost-effectiveness planes. Cost-effectiveness acceptability curves will also be estimated. Costs for the consequences of not receiving ophthalmic treatment (for example, if the patient is not able to follow up on the referral because of other health problems) will be estimated and modeled. Findings will be integrated with published reports and literature to extrapolate the findings to a national level.

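### The stated effectiveness model adjusts the binary primary outcome for neither baseline visual acuity nor home healthcare organisation, which gives up some precision and protection against chance imbalance

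*Protocol article*

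**What the plan says.** Primary outcome section: "The primary outcome is a clinically relevant change of 2 lines or more (exceeding measurement error) on the Colenbrander-1 M visual acuity chart", taken between baseline and 12 months. Study procedures places the baseline assessment, including acuity, before randomisation.

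Statistical analysis section: dichotomous outcomes are analysed with "logistic generalized estimating equation (GEE) analyses for dichotomous outcomes, given the longitudinal structure of the data", continuous ones with linear mixed models. For both, the stated predictors are: "We will use group (intervention vs. control), time, and the interaction between group and time as predictors". No covariate-adjusted analysis appears anywhere in the article.

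Randomization section: "Randomization of the clusters will be stratified by home healthcare organization", and, on team size, "we will group participating teams into matched pairs on the basis of number of participants". Study design section: "The study will be performed in collaboration with three Dutch home healthcare organizations".

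The article itself links the chance of benefit to baseline vision. The referral criteria rest on acuity worse than 0.5, and a secondary outcome counts two-line progress among participants impaired at baseline. The Background says that older people in Dutch care institutions and home healthcare "experience a high prevalence of blindness and low vision, ranging from 20 to 25" percent.

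**The concern.** A participant who already reads near the end of the chart has little room to gain two lines, and screening acts mainly through referral of those with reduced acuity. Baseline acuity is therefore likely to predict the primary outcome. Randomisation balances organisation and team size by design, but not acuity. With 10 teams per arm, the share of participants able to improve can differ between arms by chance.

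In a linear mixed model that keeps baseline as a repeated measurement, group-by-time takes up baseline differences. A two-line change does not exist at baseline, so the logistic GEE has only 6- and 12-month responses. Baseline acuity then helps to define the outcome but does not adjust the comparison. At stake are efficiency and robustness to an unlucky allocation, in a trial with few teams and few expected events.

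**Working it through.** **Inputs from the Sample size section.** 10 teams of 12 per arm; one-third dropout, leaving about 80 per arm (8 per team); proportions 0.20 and 0.05; ICC 0.02; two-sided alpha 0.05; unpooled Z-test; stated power 82%.

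**The plan's own figure.** Power = Φ(0.15 / √[(0.20×0.80 + 0.05×0.95)×DE/n] − 1.96), with DE = 1 + (m−1)×0.02 and 0.16 + 0.0475 = 0.2075.
- 120 per arm, DE 1.22: SE = √(0.2075×1.22/120) = 0.046, power 90.4%.
- 80 per arm, DE 1.14: SE = √(0.2075×1.14/80) = 0.054, power 78.8%.

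Neither is 82%; 9 completers per team (90 per arm, DE 1.16) gives about 82.7%. That mismatch is a separate matter. The unadjusted reference used here is 78.8%.

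**Expected events.** 80×0.20 + 80×0.05 = 16 + 4 = 20.

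**Gain from adjusting for baseline acuity.** The documents give no baseline-outcome association, so a range is assumed. Simulation: 20 teams of 8, one binary response, a between-team effect, logistic GEE with team-robust standard errors and a 1.96 cut-off.

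| Assumed OR per SD of baseline acuity | Unadjusted power | Adjusted power | Gain (points) |
|---|---|---|---|
| 1.0 | 78.4% | 78.1% | −0.3 |
| 1.6 | 79.7% | 80.1% | 0.3 |
| 2.7 | 79.4% | 81.7% | 2.3 |
| 4.5 | 82.1% | 87.7% | 5.5 |

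Under the null (600 runs each), rejection rates were 6% to 7% in both models up to OR 2.7. At OR 4.5 they were 7.5% unadjusted and 9.8% adjusted, so part of the largest gain may come from an uncorrected robust standard error.

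A variance formula for the standardised risk difference gives ratios of 0.97, 0.88 and 0.78 for the last three rows, and power of 80%, 84% and 88% against 78.8%. Two-group scenarios (20 to 25% impaired, 2.5 to 5% of the unimpaired changing) give 85 to 94%. They need 65% to 90% of impaired intervention participants to change two lines, so they are optimistic.

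**Chance imbalance, limiting case.** Assume that 22% are impaired, that baseline ICC is 0.02, and that all events occur among the impaired. Event rates among them are then 0.20/0.22 = 0.91 and 0.05/0.22 = 0.23. The SE of percent impaired in one arm is √(0.22×0.78×DE/n). The SD of the shift in the risk difference is that SE × √(0.91² + 0.23²) = SE × 0.94.
- 120 per arm: √(0.1716×1.22/120) = 4.2 points; shift SD 3.9 points, 26% of the 15-point target.
- 80 per arm: √(0.1716×1.14/80) = 4.9 points; shift SD 4.6 points, 31% of the target.

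Over 20% to 25% impaired, the same formula gives 4.2 down to 3.6 points at 120 per arm, and 4.9 down to 4.3 at 80.

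A milder case: 25% impaired and 5% of the unimpaired changing in both arms. The impaired then change at (0.20 − 0.75×0.05)/0.25 = 0.65 with intervention and 0.05 in control. At 80 per arm the shift SD is √(0.25×0.75×1.14/80) × (0.65 − 0.05) = 5.2 × 0.60 = 3.1 points.

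**Continuous outcomes.** With complete data and unconstrained baseline means, group-by-time reproduces the change-score comparison. At an assumed baseline-follow-up correlation of 0.7, its relative variance is 2×(1 − 0.7) = 0.60, against 1 − 0.7² = 0.51 with baseline as a covariate. The ratio is 0.85, a 15% saving.

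**The case against.** **The list may be a summary.** The sentence covers all effectiveness outcomes in a condensed article and does not say that nothing else enters. A fuller covariate set may exist in an analysis plan that is not shown. This is fair, and it means the article cannot be read as ruling adjustment out. But the article does name its predictors, so the comment is on a stated model.

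**A reader might infer bias.** The documents do not support that. The unadjusted randomised comparison is unbiased on average, and chance variation in baseline is already inside its standard error (4.6 points at 120 per arm, 5.4 at 80).

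**A reader might infer that omitting the stratification factors invalidates the standard errors.** Leaving out factors balanced by design generally makes standard errors conservative. At ICC 0.02 there is little between-team variance to recover. Stratifying without listing the stratum as a covariate is not a contradiction either.

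**A reader might put the shift above 5 points.** The SE of the between-arm gap in percent impaired is √(2×0.1716×1.22/120) = 5.9 points at 120 per arm, and 5.9 × 0.91 = 5.4. That places the whole gap in the intervention arm; spread over both arms it is 3.9.

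**The limiting case is extreme.** It needs about 91% of impaired intervention participants to gain two lines, whereas the pilot described in the Background found that only half of those referred used the referral. The primary outcome is also worded as a change, without direction, so worsening in people with good vision could count. Both points stand, and the 3.9 to 4.6 points should be read as a limiting illustration.

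**Conclusion.** The concern holds as a matter of efficiency and robustness. The stated model omits a pre-randomisation measurement that is likely to predict the primary outcome, and group-by-time does not stand in for it when the outcome is a binary change. Omitting organisation matters less, costing at most slightly conservative standard errors.

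The size is uncertain because it rests on an assumed association: a simulated power gain of about 0 to 6 points for odds ratios per SD of 1.6 to 4.5, the top of that range being the least secure. Chance imbalance could contribute an SD of 3.9 to 4.6 points to the risk difference in the limiting case, and about 3 in the milder one. Nothing here shows the planned analysis to be invalid. The change is worth making because the covariates are already available and, in the simulation, adjusting for an uninformative baseline cost almost nothing.

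**What to change.** Before outcome data are examined, prespecify in the primary logistic GEE:
- baseline logMAR acuity, defined consistently with the eye or eyes that determine the endpoint (the Primary outcome section measures both eyes and does not say which one counts);
- home healthcare organisation, as two terms for three organisations;
- team size as a single term, only if the event count allows it, and no matched-pair terms: 20 teams make 10 pairs, hence nine extra parameters against about 20 events.

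Report a standardised (marginal) risk difference, because logistic adjustment changes the odds ratio from marginal to conditional and the sample size is framed as a difference in proportions. Cluster at team level with a small-sample correction, given the null rejection rates above. In the linear mixed models, use baseline as a covariate or constrain the baseline means to be equal across arms.

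The cost is analysis-plan wording and a few degrees of freedom; no new data are needed. With about four expected control events the model must stay small, so the unadjusted result should be kept as a supporting analysis.

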### Sample size

Taking into account a potential dropout of one-third, the sample size calculation revealed that we need 120 participants in the intervention group (receiving eye screening in addition to CAU) and 120 participants in the control group (receiving only CAU). A team of community nurses who provide care to patients in a specific geographical area will form a cluster. We aim to include 10 clusters in the intervention group and 10 clusters in the control group, both with 12 subjects each (Fig. 1), but this may vary in practice depending on the willingness of patients to participate within one cluster. Based on these numbers, we will achieve 82% power to detect a difference between the group proportions of 0.15, having a clinically relevant change of two lines or more in visual acuity (primary outcome measure). The proportion in the intervention group is assumed to be 0.05 under the null hypothesis and 0.20 under the alternative hypothesis. The proportion in the control group is 0.05. The test statistic used was the two-sided *Z*-test (unpooled). The intracluster correlation was set at 0.02 [33], and the significance level of the test was set at 0.05. Based on previous research in older populations [34], we expect that we need to invite approximately 1000 patients to include 240 participants. Loss to follow-up of one-third means that 80 participants (approximately 40 in both trial arms) are allowed to dropout during the course of the study in order to estimate the abovementioned effect, which seems reasonable based on previous studies [34] (Fig. 1).

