#### Cost-effectiveness

The Institute for Medical Technology Assessment (iMTA) Medical Cost Questionnaire (iMCQ) will be used to measure healthcare utilization at baseline and after 6 and 12 months of follow-up [50]. Standard costs for health care utilization from the Dutch costing manuals will be used [51]. In addition, the costs of the intervention will be measured, including treatment uptake after referral. Treatment uptake related to eye care will also be measured and valued for the control group. Medication use is valued using prices from Dutch Medical costs guidelines [52].

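### The bootstrap specified for costs and ICERs makes no provision for the randomised nurse teams, and baseline costs and utility have no role in the comparison

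*Protocol article*

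**What the plan says.** The article's Sample size section defines the randomised unit: "A team of community nurses who provide care to patients in a specific geographical area will form a cluster". The target is 20 teams: "We aim to include 10 clusters in the intervention group and 10 clusters in the control group, both with 12 subjects each". The power calculation for visual acuity allows for this: "The intracluster correlation was set at 0.02 [33], and the significance level of the test was set at 0.05". The Randomization section adds stratification by home healthcare organisation.

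The Statistical analysis section is specific about the economic inference. For costs: "Bias-corrected and accelerated bootstrapping with 5000 replications will be used to calculate 95% confidence intervals around the mean difference in total costs". For cost-effectiveness: "Bootstrapping will be used to estimate the uncertainty surrounding the ICERs, which will be plotted graphically on cost-effectiveness planes". Then: "Cost-effectiveness acceptability curves will also be estimated". No resampling unit, team effect or covariate is named. The effectiveness models in the same section are justified by the repeated measurements and list only group, time and their interaction, so the nurse team appears nowhere in the analysis.

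Baseline data are available. Under Cost-effectiveness, the cost questionnaire is used to "measure healthcare utilization at baseline and after 6 and 12 months of follow-up". Study procedures places measurements in both groups at baseline, 6 and 12 months. The schedule table is not visible in the text at hand, so I take it that the EQ-5D-5L follows the same three visits.

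**The concern.** Cost-effectiveness is the trial's headline question, and under Patient involvement a favourable answer leads to a stakeholder conference and an implementation strategy. The economic paragraph fixes the interval type, the number of replications and the estimand, but not how the design enters. A bootstrap applied in its ordinary form treats participants as independent.

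Costs within a team are unlikely to be fully independent. Members share nurses and a geographical area. In the intervention arm, the nurse discusses the referral and follows it up with repeated motivational conversations (Referral and intervention uptake), so uptake and its cost depend partly on the nurse. Ignoring this would make intervals too narrow, the cloud on the plane too tight and the acceptability curve too steep.

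A second, distinct issue is that baseline costs and utility are strong candidates for adjustment in a trial of 20 teams, yet the plan gives them no part in the comparison.

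**Working it through.** **Plan's own figure.** None is stated for the economic analysis. The nearest is 82% power for the primary outcome. With 80 retained per arm, design effect 1.14 and the unpooled Z-test: SE = √[(0.05×0.95 + 0.20×0.80)/(80/1.14)] = 0.0544, and Φ(0.15/0.0544 − 1.96) = 78.8%. That 82% is not reproduced is a separate matter; only the ICC and team sizes are used below.

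**Inputs.** Ten teams per arm; m = 12 per team at recruitment, or 8 after the one-third loss in Sample size; ICC 0.02. No ICC is given for costs or QALYs, so 0.01, 0.05 and 0.10 are my assumptions.

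**Step 1: participants resampled as independent.** Design effect DE = 1 + (m − 1)×ICC. Estimated SE over true SE = 1/√DE. True coverage of a nominal 95% interval = 2Φ(1.96/√DE) − 1. A reported 95% probability of cost-effectiveness becomes Φ(1.645/√DE).

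| ICC | m | DE | SE ratio | Coverage | 95% becomes |
|---|---|---|---|---|---|
| 0.01 (assumed) | 8 / 12 | 1.07 / 1.11 | 0.967 / 0.949 | 94.2% / 93.7% | 94.4% / 94.1% |
| 0.02 (protocol) | 8 / 12 | 1.14 / 1.22 | 0.937 / 0.905 | 93.4% / 92.4% | 93.8% / 93.2% |
| 0.05 (assumed) | 8 / 12 | 1.35 / 1.55 | 0.861 / 0.803 | 90.8% / 88.5% | 92.2% / 90.7% |
| 0.10 (assumed) | 8 / 12 | 1.70 / 2.10 | 0.767 / 0.690 | 86.7% / 82.4% | 89.6% / 87.2% |

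A simulation (percentile bootstrap, normal data, 10 teams per arm, 1,500 runs) gave coverage at ICC 0.02 of 92.6% (m = 8) and 91.7% (m = 12) for participant resampling. It used neither BCa intervals nor skewed costs, so it checks the order of magnitude only. Unequal team sizes, which the protocol expects, were not modelled.

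**Step 2: obvious repairs.** With k = 10 teams per arm and ICC 0.02, in units of the total variance:

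- True variance of a team mean: 0.02 + 0.98/8 = 0.1425 (m = 8); 0.02 + 0.98/12 = 0.1017 (m = 12).
- Uncorrected two-stage bootstrap: (9/10) of that, plus a second dose of within-team variance, (0.98/m)×(m − 1)/m. For m = 8: 0.1283 + 0.1072 = 0.2354, and √(0.2354/0.1425) = 1.285. For m = 12: 0.0915 + 0.0749 = 0.1664, and √(0.1664/0.1017) = 1.279. Simulated SE ratios were 1.27 to 1.28.
- Whole-team resampling without correction: √(9/10) = 0.949; simulated SEs were about 6 to 7% low, with coverage of 92.1% (m = 8) and 91.4% (m = 12).

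Neither uncorrected form is adequate with 10 teams per arm.

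**Step 3: baseline values.** Adjusting for a baseline that correlates ρ with follow-up multiplies the SE by √(1 − ρ²): 0.95, 0.87 and 0.71 for assumed ρ of 0.3, 0.5 and 0.7. Omitting it therefore widens intervals.

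If QALYs are areas under the curve by the trapezoid rule at 0, 6 and 12 months (assumption), baseline utility has weight 0.25. With about 80/1.14 = 70 effective participants per arm and an assumed utility SD of 0.25, the SE of the chance baseline difference is 0.25×√(2/70) = 0.042, of which 0.25×0.042 = 0.011 QALY enters the increment directly. For SDs of 0.15 to 0.30 this is 0.006 to 0.013.

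**The case against.** The strongest defence is that the problem is partly silence. The article nowhere says that participants are resampled or that the difference is raw; a BCa interval can be placed around an adjusted difference and built on any resampling unit. A condensed article may leave such details to the full protocol or analysis plan, neither of which is shown. This stands against any claim that an individual-level, unadjusted bootstrap has been prescribed. A reader might infer that, but the text does not say it. It does not remove the point: the section sets interval type, replications, estimand and model predictors, yet omits the randomised unit throughout, although the sample size allows for it.

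A reader might also infer that ignoring baseline values makes the results too certain. It does not. Step 3 shows the effect on width goes the other way, and the 0.011 QALY is the standard error of a chance difference, already part of the sampling variance of an unadjusted comparison. It is neither expected bias nor false precision.

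Finally, the effect at the protocol's own ICC is modest, and the larger figures rest on assumed ICCs. That is correct and limits the severity.

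**Conclusion.** The point holds with limits. The economic analysis is specified without provision for nurse teams. If participants are resampled as independent, standard errors are about 6 to 10% too small and nominal 95% intervals cover about 92 to 93% at ICC 0.02. A reported 95% probability of cost-effectiveness would be about 93 to 94%. At an assumed cost ICC of 0.05, coverage is 88 to 91%. These figures are conditional on the resampling unit and on equal team sizes.

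The unused baseline costs and utility are a separate weakness: lost precision, and chance imbalance between 20 teams left in both increments. Its size depends on assumed correlations, an assumed utility SD and an assumed area-under-the-curve calculation.

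The documents do not support reading this as a demonstrated, serious overstatement of certainty. Severity: should-fix.

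**What to change.** Before analysis, specify one method that estimates incremental costs and effects jointly and respects teams:

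- a bivariate (seemingly unrelated) mixed model with team effects and a small-sample correction; or
- a two-stage bootstrap, teams then participants, with a shrinkage correction. Uncorrected, it would replace a 6 to 10% understatement of the SE with an overstatement of about 27 to 28%.

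Adjust costs for baseline costs, QALYs for baseline utility, and both for organisation. Organisation is better handled as a covariate than as a resampling stratum: with three organisations and 10 teams per arm, each stratum would hold only about three teams per arm. Run the analysis within each imputed dataset, and use the same joint replicates or model draws for the intervals, planes and acceptability curves.

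The cost is analysis programming, with no change to recruitment or data collection. Intervals widen by a factor of √1.14 = 1.07 to √1.22 = 1.10 at ICC 0.02, plus whatever the small-sample correction adds. Baseline adjustment offsets part of this: at an assumed ρ of 0.5 it multiplies the SE by 0.87. If the full protocol or analysis plan already specifies such a method, a sentence in the article's economic paragraph is enough.
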